### Drop-outs

In all survival analyses drop-out will be censored at time of drop-out. For all other analyses drop-outs will be excluded from the analyses.

- 1. Adjustment of significance and confidence interval

Indicate possible tests for multiple comparisons. Adjustment should always be considered for multiple primary outcomes. Specify details of any adjustment procedures or provide an explanation for why justification is not considered necessary.

Multiple testing correction will be performed using Bonferroni’s methods to adjust for having two primary outcomes.

- 1. Sample size calculations

The sample size of the full study will be determined based on data from the prolongation study.

- 1. Interim analysis (if relevant)

The primary outcomes will be evaluated after prolongation phase.

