# List of used acronyms and abbreviations

| **Abbreviation** | **Term/Explanation** |
| --- | --- |
| ACE2 | Angiotensin-converting enzyme 2 |
| AE | Adverse Event = any untoward medical occurrence |
| AR | Adverse Reaction = adverse event, that is each unfavorable and unexpected reaction to a study treatment, regardless of dose |
| CNS | Central nervous system |
| CRF | Case Report Form |
| DSMB | Data Safety Monitoring Board |
| DSUR | Development Safety Update Report = annual safety report |
| EPM | Etikprövningsmyndigheten (English: Swedish Ethical Review Authority) |
| GCP | Good Clinical Practice |
| ICH | International Council for Harmonization |
| ICU | Intensive care unit |
| ITT | Intention-to-treat = including all data from all subjects who have participated in the study |
| LVFS | Läkemedelsverkets författningssamling (English: Swedish Medical Products Agency’s statutes) |
| MPA | Swedish Medical Products Agency |
| PCR | Polymerase chain reaction |
| PP | Per Protocol analysis = including only data from subjects who have completed the study completely in accordance with the protocol, with no deviations from the protocol |
| SAE | Serious Adverse Event = serious untoward medical occurrence |
| SPC or SmPC | Summary of Product Characteristics |
| SUSAR | Suspected Unexpected Serious Adverse Reaction |
| TMPRSS2 | Transmembrane protease, serine 2 |

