## Withdrawal criteria

Subjects can discontinue their participation in the study at any time without any consequence to his/her continued treatment. The investigator/sponsor can at any time terminate the study for a subject due to, e.g., unacceptable adverse events/adverse reactions or because the subject does not follow procedures in the study protocol. If the subject discontinues the study, follow-up of this subject will be performed according to the clinic’s routine.

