**Mortality at 6 months**

Death due to any cause and death date will be found by the study nurse through the medical records or by death registry.

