# Statistics

## Analysis population

Two efficacy analysis sets will be used: the ‘all patients treated’ set which will be analyzed according to the intention-to-treat (ITT) principle and it is therefore called the ITT set and the ‘per protocol’ (PP) set. The primary and secondary statistical analysis will be based on the ITT set. In addition, an analysis of the efficacy variables will also be carried out on the PP set in order to detect any sensitivity in the results obtained from the ITT analysis. At the clean file meeting it will be decided whether a patient will be included in the ITT and/or PP population. Also, a safety analysis set will be used for the assessment of the safety variables.

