***The ITT analysis set***
All randomized subjects will be included in the ITT analysis set.

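### The drop-out rule contradicts the protocol's own ITT and safety sets, and permits informative censoring of the two primary outcomes

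*Protocol*

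**What the plan says.** Section 10.1 states: "The primary and secondary statistical analysis will be based on the ITT set". It defines that set plainly: "All randomized subjects will be included in the ITT analysis set". The abbreviation list explains ITT as "including all data from all subjects who have participated in the study". The safety set is also all randomised subjects and is declared identical to the ITT set.

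Section 10.2.1 (Drop-outs) gives two rules. For time-to-event analyses: "In all survival analyses drop-out will be censored at time of drop-out". For everything else: "For all other analyses drop-outs will be excluded from the analyses". No exception is made for safety, and the protocol does not define drop-out.

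Section 6.4 (Withdrawal criteria) says how a patient may leave. Subjects may leave by their own choice. The investigator or sponsor may also end the study for a subject, for example for unacceptable adverse events or reactions, or "because the subject does not follow procedures in the study protocol". What follows is: "If the subject discontinues the study, follow-up of this subject will be performed according to" the clinic's routine, which is not the trial schedule.

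Section 8.1.2 (Mortality at 6 months) shows that at least one outcome needs no study visit: the "death date will be found by the study nurse through the medical records or by death registry".

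**The concern.** An analysis set of all randomised subjects and a rule that deletes some of them cannot both be carried out. The conflict covers every non-survival analysis in section 10.2.1, including the comparison of adverse events by Fisher's exact test.

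Safety is the most exposed. A patient removed because of an adverse event has, by definition, had one. Deleting that patient removes a known event from the result. Section 5 gives detection of unexpected serious effects as the purpose of the explorative phase, and safety is a condition for moving to each later phase.

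The two primary outcomes, time to ventilation or death and time to discharge, are Cox analyses, so drop-outs are censored and not deleted. The risk here is informative censoring. Patients who leave may have a different prognosis, the trial is non-blinded so removal is decided with the arm known, and outcomes that could still be found are not used.

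**Working it through.** The protocol states no drop-out rate, event rate or power, so it has no figure of its own to reproduce. Every rate below is an assumption.

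**1. The sections side by side.**

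- Sections 10.1 and 10.2.1: all randomised subjects are in the ITT set used for secondary analyses, yet drop-outs are excluded from all non-survival analyses. These conflict directly.
- Safety set and 10.2.1: all randomised subjects are in the safety set, yet the Fisher comparison of adverse events is a non-survival analysis with no exemption. These also conflict.
- Sections 6.4 and 10.2.1: a patient whose participation is ended for an adverse reaction has discontinued the study. On the ordinary meaning of drop-out, the patient is then deleted from the adverse event table and censored in the Cox models.
- Sections 8.1.2 and 10.2.1: the death date can be found from records or the registry, yet the censoring rule stops at drop-out even when a later death is known.

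**2. Effect on the adverse event rate.** Let a be the true proportion of enzalutamide patients with an event and d the proportion of the arm withdrawn because of one. All withdrawn patients are events, so after deletion the observed rate is (a − d)/(1 − d). With a = 20%:

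- d = 2%: 0.18/0.98 = 18.4%
- d = 5%: 0.15/0.95 = 15.8%
- d = 10%: 0.10/0.90 = 11.1%

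No assumption about prognosis is needed.

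**3. Effect on ventilation or death, with no true treatment effect.** This is a two-proportion approximation that treats drop-outs as leaving before their event. Let p be the true risk in both arms, d the drop-out share in an arm and q the risk among drop-outs.

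- Observed risk in an arm = (p − d·q)/(1 − d)
- HR = ln(1 − enzalutamide risk)/ln(1 − control risk)

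Worked example with p = 20%, q = 50% and drop-out 5% against 1%: enzalutamide (0.20 − 0.025)/0.95 = 0.1842; control (0.20 − 0.005)/0.99 = 0.1970; HR = ln(0.8158)/ln(0.8030) = 0.93.

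The last column is the chance of a significant result favouring enzalutamide at N = 600 (400:200). It uses a pooled z test and a two-sided level of 0.025 per outcome, that is, an assumed overall 0.05 with Bonferroni over two outcomes. The nominal value is 1.25%.

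| p | Drop-out, enzalutamide vs control | q | HR | False positive |
|---|---|---|---|---|
| 20% | 5% vs 5% | 50% | 1.00 | 1.25% |
| 20% | 5% vs 1% | 20% | 1.00 | 1.25% |
| 20% | 5% vs 1% | 40% | 0.95 | 2.4% |
| 20% | 5% vs 1% | 50% | 0.93 | 3.2% |
| 20% | 10% vs 2% | 40% | 0.90 | 4.5% |
| 20% | 10% vs 2% | 50% | 0.85 | 7.9% |
| 10% | 5% vs 1% | 50% | 0.82 | 6.6% |
| 10% | 10% vs 2% | 50% | 0.59 | 28% |
| 20% | 5% vs 10% | 50% | 1.12 | 0.3% |

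The HR stays at 1.00 when drop-out is equal with equal prognosis, or unrelated to risk. It falls to about 0.9 when drop-out is heavier on enzalutamide and high-risk, and lower only at the extreme of the assumed range. With heavier drop-out on control (last row) it moves against enzalutamide. Time to discharge was not modelled.

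**The case against.** A reader might infer that the rule removes failures mainly from the enzalutamide arm and so favours the drug on every outcome. The documents do not support that. A reaction to enzalutamide can arise only in arm 1, but section 6.4 gives its reasons as examples and also covers leaving by choice, adverse events of any kind, and not following any study procedure. Swabs, blood samples and visits apply to both arms, adverse events are recorded for all patients, and control patients in an open-label trial may leave too. No drop-out figures by arm are given. For hormonal status or serology, a bias in favour of the drug has no clear meaning.

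Three further points stand. First, censoring a patient whose later outcome is truly unknown does not breach ITT, because the patient remains in the set up to that time. Second, stopping enzalutamide at discharge or ventilation (section 7.8) is a planned treatment stop and is not described as leaving the study. A narrow reading of drop-out as loss to follow-up or withdrawn consent is therefore possible. Third, follow-up does not cease: clinic-routine care continues, deaths are traceable, and section 9.4 still requires serious events considered related to treatment to be reported after trial termination.

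The moderate hazard ratio shifts are also small against sampling error. At N = 600 and 20% risk there are about 120 events, so the standard error of log HR is about 1/√(120 × 2/3 × 1/3) = 0.19. An HR of 0.93 (log −0.075) is about 0.4 of that.

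These points limit the claim about the primary outcomes. They do not remove the contradiction between 10.1 and 10.2.1. The narrow reading of drop-out is not written anywhere, and the data that remain available are those the rule would not use.

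**Conclusion.** The drop-out rule is wrong as written for the non-survival analyses. It contradicts the ITT set and the safety set, and taken literally it leaves patients removed for an adverse reaction out of the adverse event comparison. The size depends on how many are removed: at an assumed true rate of 20%, the observed rate falls to between 18.4% and 11.1% when 2% to 10% of the arm is withdrawn for an event. This rests on counting a patient removed under section 6.4 as a drop-out, which is the ordinary meaning of an undefined term.

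For the two primary outcomes the finding is narrower. The rule permits informative censoring that may differ between arms, and it ignores outcomes that can be retrieved. Bias requires drop-out that is both unequal and related to prognosis. Neither is documented, so direction and size are unknown and the hazard ratios above are conditional illustrations. The contradiction should be corrected because the plan as written could give a wrong safety result, the correction is cheap, and follow-up that is not collected may be hard to recover later.

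**What to change.** - In 10.2.1, define drop-out as withdrawal of consent to data collection or loss to follow-up only.
- In 6.4, state that stopping study drug, for any reason and by anyone's decision, is not leaving the study.
- Unless consent to data use is withdrawn, keep collecting ventilation, discharge, readmission and death from medical records and the registry, to day 30 or 45 as each endpoint requires and to 6 months. Censor only where the outcome truly cannot be obtained.
- Replace the exclusion sentence with: all randomised subjects are analysed using all available data, and all are kept in the safety analysis.
- Add a sensitivity analysis for truly missing outcomes, such as multiple imputation or a worst-case assignment.

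The cost is protocol wording, one line in the consent form and a few chart look-ups.

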# Quality Control and Quality Assurance

## Quality Assurance and Sponsor oversight

It is the investigators responsibility that the CRFs are reviewed for completeness and accuracy. It is also the investigators responsibility to ensure compliance with GCP and all applicable regulatory requirements. Regulatory agencies may conduct a regulatory inspection of this trial. Such audits/inspections can occur at any time during or after completion of the trial. If an audit or inspection occurs, the investigator and institution agree to allow the audit/inspection.

## Monitoring

The study will be monitored by an independent monitor before the study begins, during the study conduct, and after the study has been completed, so as to ensure that the study is carried out according to the protocol and that data is collected, documented, and reported according to ICH-GCP and applicable ethical and regulatory requirements. Monitoring is performed as per the study’s monitoring plan and is intended to ensure that the subject’s rights, safety, and well-being are met as well as data in the CRF are complete, correct, and consistent with the source data.

To verify this, the study will be monitored in a systematic, prioritized, risk-based approach consistent with the demands of the trial and site activity. If any misconduct or neglect would be notified the sponsor and investigator will be notified for corrective and preventive actions.

The investigator and the head of the medical institution (where applicable) agrees to allow the monitor access to all relevant documents.

Data monitoring will be performed regularly, by either monitoring at site at a computer not in the same wards as COVID-19 positive patients, or by phone and or video conference with the monitor with direct access to the database with the eCRF and personal at the hospital.
Monitoring details will be specified in the study monitoring plan.

## Source data

The investigator must keep source documents for each subject in the study. A document describing what has been classified as source data in the study should be included in the Investigator Site File (ISF). The investigator must ensure that all source documents are accessible for monitoring and other quality control activities.

Source data is defined before study start at each individual site.

The investigator must ensure that all source documents are accessible for monitoring and other quality control activities. The monitor will have access to medical records and source data after secrecy agreement have been signed by the responsible party at the site as well as by the monitor. Subjects have provided consent by signing the Subject Information and Informed Consent form where this is specified.

## Deviations or serious breaches

Serious breaches and deviations from the study protocol, GCP and other regulations that significantly and directly affects, or with high likelihood could affect, the subjects in Sweden or the scientific value of the study, shall be immediately reported within 7 days (from knowledge) to the Swedish Medical Products Agency. It is the sponsor’s responsibility to judge the consequences of deviations that have occurred, and thus also to decide whether the Swedish Medical Products Agency should be informed.

Minor deviations that do not affect subjects’ integrity or safety, nor significantly affect the study’s scientific value, are documented in the study documentation of the principal investigator and the sponsor.

## Audits and inspections

Authorized representatives for the sponsor and Competent Authorities (CA) may carry out audits or inspections at the study site, including source data verification. The investigator must ensure that all source documents are available for audits and inspections. The purpose of an audit or inspection is to systematically and independently review all study-related activities and documents, so as to determine whether these activities were performed, registered, analyzed and reported correctly according to protocol, Good Clinical Practice (GCP) and applicable regulations.

# Ethics

## Compliance to the protocol, GCP and regulations

The study will be performed in compliance with the study protocol, the Declaration of Helsinki, ICH-GCP (Good Clinical Practice) guidelines and current national and international regulations governing this clinical trial. This is to ensure the safety and integrity of the study subjects as well as the quality of the data collected.

## Ethical review of the study

The final study protocol for clinical trials must be approved, as a part of the application for a permit for clinical trials, by both the Swedish Ethical Review Authority (Etikprövningsmyndigheten, EPM) and the Swedish Medical Products Agency before the trial can be conducted. The final version of the informed consent form and other information provided to subjects, must be approved or given a written positive opinion by EPM. EPM and the Swedish Medical Products Agency must be informed of any changes in the study protocol in accordance with current requirements.

## Procedure for obtaining informed consent

The principal investigator at each site shall ensure that the subject is given full and adequate oral and written information about the study, its purpose, any risks and benefits as well as inclusion and exclusion criteria. Subjects must also be informed that they are free to discontinue their participation in the study at any time without having to provide a reason. Subjects should be given the opportunity to ask questions and be allowed time to consider the provided information. If the person chooses to participate, both the subject and the investigator shall sign the informed consent form. A copy of the subject information as well as the informed consent form shall be provided to the subject. Due to the risk of contamination, the signed informed consent will be photographed and assessed as source data. Local variations on this procedure are allowed. The subject’s signed and dated informed consent must be obtained before performing any study-specific activity in the study. Each subject who participated in the study will be identified by a subject number on a subject identification list. The subject agrees that monitors, auditors, and inspectors may have access to their medical records and other source data. If new information is added to the study, the subject has the right to reconsider whether he/she will continue their participation.

## Data protection

If any part of the data is handled by any other organization, inside or outside the EU, appropriate agreements and/or other documentation will be established, to ensure that the data processing is performed in accordance with the provisions of the General Data Protection Regulation (GDPR) and other relevant legislation, before any data transfer takes place.

The content of the informed consent form complies with relevant integrity and data protection legislation. In the subject information and the informed consent form, the subject will be given complete information about how collection, use and publication of their study data will take place. The subject information and the informed consent form will explain how study data are stored to maintain confidentiality in accordance with national data legislation. Data collected in the eCRF REDCap will be stored at secure servers at Umeå University. All information processed by the sponsor will be pseudonymized and identified with study ID.

The informed consent form will also explain that for verification of the data, authorized representatives of the sponsor, as well as relevant authority, may require access to parts of medical records or study records that are relevant to the study, including the subject’s medical history.

## Insurances

Study subjects are insured through Swedish patient insurance as well as the Swedish pharmaceutical insurance.

# Substantial changes to the study

Substantial changes to the signed study protocol are only possible through approved protocol amendments and by agreement from all responsible persons. Information on non-substantial changes should be clearly noted in the amended protocol.

In the event that substantial changes to the protocol (e.g., changing of the main objective, primary or secondary variables, method to measure the primary variable, changing of the investigational product or dosage) will be made during the course of the study, approval from the Swedish Ethical Review Authority (Etikprövningsmyndigheten, EPM) as well as the Swedish Medical Products Agency (Läkemedelsverket) shall be obtained before any changes are implemented. A change that concerns a new site, new investigator or a new study patient information sheet shall only be approved by EPM.

Non-substantial changes will be recorded and later entered in documentation that is submitted, for example in any subsequent notifications of a substantial change or in connection with End of Trial reporting.

The investigator must not make any deviation from or change of the protocol, except if necessary to eliminate an immediate risk to the study subjects.

# Collection, handling, and archiving data

Subjects who participate in the study are coded with a specific study identification number. All subjects are registered in a subject identification list (subject enrolment and identification list) that connects the subject’s name and personal number with a study identification number.

All data will be registered, managed, and stored in a manner that enables correct reporting, interpretation, and verification. The complete Trial Master File, as well as source documents, will be archived for at least *15* years after the study is completed. Source data in the medical records system is stored and archived in accordance with the respective hospital regulations.

## Case Report Form (Forskningspersonsformulär)

An electronic Case Report Form (eCRF), REDCap, is used for data collection. The investigator must ensure that data is registered and any corrections in the CRF are made as stated in the study protocol and in accordance with the instructions. The investigator must ensure that the registered data is correct, complete, and that reporting takes place according to the timelines that have been predefined and agreed. The investigator signs the completed CRF. A copy of the completed CRF will be archived at the study site.

If an examination/test is not performed and data does not exist, ND (Not done) or NK (Not known) is marked. If the question is irrelevant NA (Not applicable) is written. Corrections in the paper CRF/working sheets are done by striking out the incorrect information and adding the correct information next to the incorrect information, signing, and dating the correction.

# Notification of study completion, reporting, and publication

The Swedish Medical Products Agency shall be informed of the study’s completion at latest 90 days after study end, through submission of a ”Declaration of End of Trial Notification” form.

Within one year after the study is completed, the results shall be analyzed, a clinical study report with individual data shall be prepared, and the study results shall also be reported in the EudraCT database.

